## **Reporting period for adverse events**

All AEs, irrespective of nature, will be followed until resolution or until end of the follow-up period.

The reporting period for AEs starts at inclusion and ends at the final follow-up visit 2 months after inclusion.

## **Sponsor's reporting of serious adverse drug reactions and suspected unexpected serious adverse reaction**

The investigator or designee have to make a causality (relationship) assessment. The term SADR (Serious Adverse Drug Reaction) is to be used when the Investigator deems the SAE as possibly or probably related to the IMP. Serious Adverse Drug Reactions are to be reported annually to the MPA and the ethical committee.

If the event is not described before, e.g. in the SmPC, the event is a SUSAR (Suspected Unexpected Serious Adverse Reaction). The sponsor has the obligation to submit a SUSAR report to the Swedish Medical Products Agency (via a CIOMS-form) and to the Stockholm Regional Ethical Review Board within:

- 7 days if fatal or life-threatening (follow-up information within an additional 8 days)
- 15 days if non-fatal and non-life-threatening (follow-up information as soon as possible)

The sponsor has the obligation to, once a year throughout the clinical study (or on request); submit a safety report to the MPA and the IEC taking into account all new available safety information received during the reporting period.

## **Stopping rules**

If an attending physician assesses that a patient is suffering from an adverse event induced by the IMP and requiring treatment, IMP treatment will be stopped for that patient. The outcome will be classified as an adverse event necessitating treatment stop.

A study subject can terminate his/her participation in the study at any time without giving a reason why. Should a subject wish to do so he/she will be treated in line with standard recommendations.

Study organisers can end a patient's participation for safety reasons.

If a patient is excluded, already collected data will be used in subsequent analyses unless he/she objects.

## **Study management**

### **Independent Data Safety and monitoring board (DSMB)**

No DSMB is required as the IMP is safe and well characterised at the dose used and as the study is of short duration, not blinded, the subjects are adults and are not suffering from a life threatening illness.

### **Clinical monitoring**

Before the initiation of the study, the monitor will:

- Determine the adequacy of the facilities.
- Discuss with the investigator and study personnel their responsibilities with regard to CSP adherence, local regulations, and the duties of monitor.
- At an initiation meeting, the monitor will comply with the ICH-GCP Guidelines (ICH-GCP 8.3.20) and document that the study procedures were reviewed with the investigator and the investigator's staff.

During the study, a monitor will pay visits to the investigational site in order to:

- provide information and support to the Investigator.
- confirm that facilities remain acceptable.

- confirm that the investigational team is adhering to the CSP.
- confirm that data are being accurately recorded in the CRFs.
- ensure that accountability checks for the IMP are being performed.
- conduct source data verification, which will require direct access to all original records for each subject (e.g. medical records).

The monitor will be available (by phone, and e-mail) between visits whenever the investigator or other study personnel at the investigational site needs information, advice or help.

All documentation and correspondence pertaining to the study (raw data, letters etc.) should be kept in accordance with ICH-GCP.

### **Audits and inspections**

The purpose of an audit or inspection is to systematically and independently examine all study related activities to document that they were conducted, recorded, analyzed and accurately reported according to the CSP and the background regulatory demands.

Audits or inspections may therefore be performed at the study site during or after the study. Visits may thereby be paid by the sponsor or by the MPA. These visits may include source data verification and confidentiality documents are therefore created.

The Investigator should contact the monitor immediately if they are contacted by the MPA about an inspection at their study site.

### **Training of study personnel**

The investigator will maintain records of all individuals involved in the study (medical, nursing and other personnel). The investigator will ensure that appropriate training relevant to the study is given to the personnel involved in the study, and that any new information of relevance to the conduct of the study is forwarded to the persons involved.

### **Changes to the study protocol**

Study procedures will not be changed without mutual agreement between the investigators.

If the clinical study protocol (CSP) needs to be substantially amended, the amendment or a new version of the CSP must be approved by the MPA and the ethical committee before implementation. Approval must also be obtained for the written Patient Information and Informed Consent Form, if applicable.

If an amendment to the CSP substantially alters the study design, or increases the potential risk to the patients, written informed consent must be obtained again for currently enrolled patients and must be provided to additional patients prior to their entry into the study.

If the amendment only involves a new study site, new investigator or new Patient Information, approval must only be approved by the ethical committee.

### **Protocol deviations**

Deviations from the CSP, deemed necessary for an individual subject, will be reported in the CRF giving the reason and date. If necessary, the investigator (or designee) will contact the monitor to inform about the deviation.

### **Study reporting**

After completion of the study, the Investigator will prepare a clinical study report. The Investigator is responsible for submitting the final study report to the MPA.

### **Archiving**

The Investigator shall keep records of the study for 10 years after final signed 12-month Clinical Study Report. This includes any original source documents related to the study, including the subject Identification List with Subject Numbers, full names and the original signed informed consent forms. The sponsor should be contacted before any study related documentation is planned for destruction.

### **Patient confidentiality**

The patients have the right to request access to his/her personal data and the right to request rectification of any data that is not correct and/or complete. Investigator or designee personnel whose responsibilities require access to personal data agree to keep the identity of each patient confidential. This agreement is to be substantiated in a separate document.

### **Insurance**

Participants are covered by "patientskadelagen" and the investigational medicinal product betamethasone is covered by "läkemedelsförsäkringen".

### **Publication**

The investigator is responsible for registering the study in a publicly accessible database before recruitment of the first patient.

The study report may form the basis for a manuscript intended for publication in a medical journal. Attempts to publish negative or inconclusive as well as positive results must be made, or otherwise made publicly available.

### **Quality control (QC) and quality assurance (QA)**

This study will be conducted in compliance with this protocol, standard operating procedures at the study site, the ICH Guideline for GCP and any local regulations.

Audit of the study sites may be conducted to assess and help assure compliance with GCP and applicable regulatory requirements. The study sites may be subject to a QA audit by the sponsor or its representatives, as well as this study may be reviewed by an independent QA department and/or inspected by regulatory authorities. This implies that auditors/inspectors will have the right to inspect the study sites at any time during and/or after completion of the study and will have access to source documents, including patients' medical records. By participating in this study, the investigator agrees to this requirement.

### **Ethical considerations**

The trial has been registered with the EU's electronic database of clinical trials (EudraCT), with EudraCT number 2016-002585-32, and sponsor protocol number mpp01. The trial will be submitted to the Swedish Medical Products Agency (läkemedelsverket) and Regional Ethical Review Board in Stockholm for review. Following approval, the study will be started. Patients will be informed of the study verbally and in writing. Details about the trial including risks and benefits will be explained and any questions answered. A copy of the written consent form will then be signed.

The trial will be conducted in compliance with this protocol, the ICH guidelines for Good Clinical Practice, the latest edition of the Declaration of Helsinki and any local regulations.

### **Statistics**

Power calculation: Was done using [www.sealedenvelope.com](http://www.sealedenvelope.com). The significance level was set at 5% and the power at 90%. In the only randomised trial available, cortisone versus not cortisone resulted in defervescence by 48 hours in 100% and 0% respectively and hypoxemia lasted for a mean <2 versus >3 days, respectively. Our power calculation therefore assumes resolution of hypoxemia by 48 hours in 95% of participants with betamethasone and 65% of those without betamethasone. The sample size required in each group would then be 33. Assuming a 5% loss to follow up 70 patients need to be included.

Duration: Approximately one year for patient inclusion and follow up. The trial will end after the last visit of the last subject. A Declaration of End of Trial Notification will be sent to the MPA at the latest 90 days after the study has ended.

Data storage: All CRFs and signed informed consent forms will be collected from all study sites and stored in a locked cupboard in a locked room at Danderyd hospital for at least 10 years. Data will be double entered using EpiData 3.1 by the investigators at Danderyd Hospital. Study ID only will be used on computerised records. The key will be stored with the CRFs at Danderyd Hospital.

Data analysis: The data will be analysed using survival estimates of the primary endpoint. A per protocol and intention to treat analysis will be done. Loss to follow up will be censored at the time of loss to follow up. Final analysis will include a description of included participants, proportions of adverse events and any serious adverse events, the proportion of participants withdrawn or lost to follow up, the cumulative success and failure rates by week 8. Categorical variables will be compared using the  $\chi^2$  test or Fisher exact test and continuous variables using quantile regression.

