### **Study Procedures**

Randomisation: All participants will be randomised to either a treatment group or a control group (A or B) using [www.sealedenvelope.com](http://www.sealedenvelope.com). Randomisation is blocked (using random permuted blocks) with 1:1 allocation ratio to ensure that the groups are balanced periodically.

Treatment: All participants will take doxycycline (ATC J01AA02) 200 mg once daily until 10 days total effective treatment has been taken. If participants have been treated with active antibiotics before inclusion, treatment will be switched to doxycycline upon inclusion. Total effective antibiotic treatment duration will be 10 days. The doxycycline dose chosen is slightly higher than normal as the doxycycline minimal inhibitory concentration is very similar to that obtained when 100 mg is given daily. The treatment duration is ten days as this group of patients have complicated mycoplasma pneumonia.

Participants randomised to treatment with betamethasone will take 3 mg once daily days 1 and 2 and 2 mg once daily days 3, 4 and 5, given orally according to the SmPC.

Betamethasone intake will be observed whilst admitted and confirmed by questioning thereafter. After discharge, any remaining doses will be labelled with dose information as done in standard clinical practice and given to the patient to take at home.

The betamethasone dose has been selected based on clinical experience, similarity to that used for treatment of exacerbations of chronic obstructive pulmonary diseases and asthma, tolerability and likely acceptance by clinical practitioners.

Betamethasone (ATC H02AB01) is a corticosteroid with a Marketing Authorization in Sweden (MA number 6940). It will be provided free of charge to participants and taken from

the pharmaceutical store room of the ward. As the drug only is administered directly from the ward, no study specific marking - except dose to be taken - is needed.

Patients randomised to the control group will only receive standard care with doxycycline as described above.

Monitoring and follow up: Whilst admitted breathing rate, peripheral oxygen saturation (measured with pulse oximetry after 20 minutes of rest), oxygen use, pulse, blood pressure, body temperature, peak expiratory flow and mental state will be monitored three times daily and entered into computerised medical records.

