Medical records will be searched to determine values prior to inclusion in the study and data will be entered on to clinical records form B (appendix 2). Chest x-rays or CT scan will have been performed routinely prior to inclusion.

Following inclusion, participants will also be followed up with structured questionnaires (appendix 3, 4 and 5) to identify the community acquired pneumonia (CAP) score on days 1, 2, 3, 4, 5, 6, 7, 14, 28, 42 and at 2 months after inclusion. If the patient has been discharged, physiological parameters will not be recorded but the CAP score will be obtained per telephone. The CAP score is a disease-specific activity score for community acquired pneumonia; it ranges from 0 to 100, 0 marking the worst and 100 the best score (10).

Blood samples for analysis of C-reactive protein (CRP), white blood cell count (WBC) and haemoglobin (Hb) will be taken daily until normalised or discharge from hospital and on day 28. Fasting blood glucose and blood samples for immunological analyses will be taken daily until discharge and on day 28. Blood samples for *M. pneumoniae* serology will be taken on the day of inclusion and at day 28. A sample for diagnostic PCR and for subsequent phenotypic and genotypic characterisation of *M. pneumoniae* bacteria will be taken from upper airways prior to inclusion, upon inclusion and on day 28. Samples will be frozen at -80°C until phenotypic and genotypic characterisation. Patients will be discharged from the hospital at the discretion of treating physician. Follow up visits will be done on day 28 and by phone on days 42 and 56.

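### The protocol's primary analysis names no baseline covariate, although baseline respiratory values are recorded; adjustment adds little power at the design effect but could add more if the true effect is smaller

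*Protocol*

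**What the plan says.** On the primary endpoint, time to resolution of hypoxemia, the data analysis paragraph of the Statistics section says "The data will be analysed using survival estimates of the primary endpoint". It names no test, model or covariate. The other methods listed there (chi-square or Fisher exact test, quantile regression) also come without covariates.

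On allocation, Study Procedures says "Randomisation is blocked (using random permuted blocks) with 1:1 allocation ratio to ensure that the groups are balanced periodically". No stratification factor is named. Study Design lists 14 hospitals.

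On baseline data, the monitoring text in Study Procedures lists breathing rate, saturation and oxygen use among the measures taken, and then states "Medical records will be searched to determine values prior to inclusion in the study", with entry on form B. On earlier antibiotics the treatment text says "If participants have been treated with active antibiotics before inclusion, treatment will be switched to doxycycline upon inclusion", with ten days of effective treatment in total.

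The power calculation "assumes resolution of hypoxemia by 48 hours in 95% of participants with betamethasone and 65% of those without betamethasone". It continues: "The sample size required in each group would then be 33". And: "Assuming a 5% loss to follow up 70 patients need to be included".

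**The concern.** The natural reading of survival estimates by arm is an unadjusted comparison. The values left out are close relatives of the endpoint. Entry requires a saturation below 93% and a breathing rate above 20. The event is a saturation above 92% without oxygen and a breathing rate of 20 or less. Baseline saturation, oxygen need and breathing rate therefore measure how far each patient starts from the event, and it is plausible that they predict its timing.

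Permuted blocks balance the numbers per arm, not severity. Two things are at stake. The first is power, because leaving a prognostic factor out of a survival comparison pulls the hazard ratio towards 1. The second is credibility, because in a small open trial covariates chosen after a chance imbalance has been seen would persuade few readers.

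**Working it through.** **Inputs from the protocol.** 48-hour rates 95% and 65%; 5% significance (two-sided assumed, since sidedness is not stated); 90% power; 33 per group; 5% loss; 70 in total.

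**Input assumed.** The prognostic strength of the baseline covariates is not in the protocol. It is taken as a log hazard ratio per standard deviation (SD) of a combined index of 0, 0.3, 0.5 and 0.8.

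**1. The protocol's own figure.** Two proportions, unpooled variance:

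n = (1.960 + 1.282)² × (0.95×0.05 + 0.65×0.35) / 0.30² = 10.51 × 0.275 / 0.09 = 32.1, so 33 per group. Then 66 / 0.95 = 69.5, so 70. Both figures reproduce.

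**2. Power of an unadjusted survival analysis at the design effect.** With exponential times, HR = ln(0.05)/ln(0.35) = 2.85, and ln HR = 1.049. Schoenfeld's formula gives power = Φ(√events / 2 × ln HR − 1.96).

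- All 66 resolve: 4.062 × 1.049 − 1.96 = 2.30, power 98.9%.
- Follow-up cut at 48 hours, 33 × (0.95 + 0.65) = 53 events: 3.640 × 1.049 − 1.96 = 1.86, power 96.8%.
- Smallest HR with 90% power at 66 events: exp(3.242 / √16.5) = 2.22.

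**3. What adjustment adds.** Simulation with 33 per arm, exponential times, two baseline covariates and 1,500 trials per setting. The marginal 48-hour rates were held fixed, so that the treatment effect does not shrink as the covariates grow stronger. Patients were followed until resolution.

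| True 48 h rates | Log HR per SD | Log-rank | Adjusted Cox | Change (points) |
|---|---|---|---|---|
| 95% v 65% | 0 | 98.5% | 98.1% | −0.4 |
| | 0.3 | 98.8% | 99.3% | +0.5 |
| | 0.5 | 98.5% | 99.6% | +1.1 |
| | 0.8 | 98.7% | 100.0% | +1.3 |
| 90% v 65% | 0 | 86.7% | 85.7% | −1.0 |
| | 0.3 | 87.1% | 89.3% | +2.2 |
| | 0.5 | 87.9% | 95.2% | +7.3 |
| | 0.8 | 87.9% | 98.9% | +11.0 |
| 85% v 65% | 0 | 67.5% | 67.4% | −0.1 |
| | 0.3 | 62.3% | 67.8% | +5.5 |
| | 0.5 | 62.2% | 73.5% | +11.3 |
| | 0.8 | 64.3% | 88.1% | +23.8 |

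Monte Carlo error is about 0.3 points near 98% and 1.2 points near 65%. With follow-up cut at 48 hours, the changes run from −0.4 to +1.2, −0.6 to +11.3 and −1.7 to +19.2 points for the three effects. A second simulation on the same footing gave about 0 to 1.5, 0 to 10 and 0 to 25 points, and a loss of at most about 2 points with three covariates of no prognostic value.

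**4. Type I error** (3,000 trials, no effect). Adjusted Cox 5.7 to 5.8%; log-rank 5.0 to 6.2%.

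**5. Chance imbalance.** With 33 per arm, a standardised baseline difference has SD √(2/33) = 0.246. A difference above 0.3 SD corresponds to |z| > 1.22, about 22% of trials for one covariate. For at least one of three independent covariates it is 1 − 0.78³, about 53%. At a log HR of 0.5 per SD, a 0.3 SD imbalance moves the log HR by 0.15. The standard error of the log HR is about 2/√66 = 0.25.

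**The case against.** The strongest reply is that the protocol's sentence decides nothing. A reader might infer that the protocol rejects adjustment, but it neither names nor excludes a covariate. Covariates are often left to a statistical analysis plan, and none was available here. This stands: the point is a recommendation to fix the model, not an error in the text.

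A reader might also infer that the trial as designed is losing power. It is not. At 95% against 65% the unadjusted analysis is well above the 90% asked for. Larger contrasts appear if the conditional hazard ratio is held at 2.0, with the 65% control rate set at the covariate mean: 63% to 76% at 0.5 per SD, and 49% to 76% at 0.8. But an HR of 2.0 lies below the design value of 2.85, and that set-up shrinks the marginal effect as the covariate strengthens. The fall in unadjusted power from 63% to 49% comes from that shrinkage.

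A third tempting inference is that prior antibiotic days are already on the case record form. The protocol gives a switching rule and a total duration, so the days must be known, but it does not say that they are recorded. The forms are appendices that are not shown.

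Two further replies carry part weight. The entry criteria narrow the baseline range, which may weaken prediction; they cap only the mild end and set no lower limit on saturation or upper limit on breathing rate. Chance imbalance is not bias, and the unadjusted standard error already allows for it. That is true, but it does not remove the reason for choosing covariates in advance.

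**Conclusion.** The point holds as a modest, low-cost recommendation. The protocol names no covariate and no stratification factor, while it records baseline values of the endpoint itself.

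The gain depends on the true effect. At the protocol's own effect it is at most about 1.5 points on a base of about 98%. At 85 to 90% against 65% it is about 0 to 25 points. A smaller effect is a realistic case: the design effect is drawn from a trial in children with refractory disease, and the protocol itself says that the steroid doses studied were high and that data in hospitalised adults are lacking.

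The result rests on exponential times, a correctly specified model and an assumed prognostic strength of 0 to 0.8 per SD. At the lower end of that range there is nothing to gain.

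**What to change.** In the data analysis paragraph of the Statistics section, state the primary analysis as a Cox model of time to resolution with treatment plus two baseline covariates: the last pre-randomisation saturation or oxygen need (choose one and define it), and breathing rate. Add days of effective antibiotic before inclusion only if the case record form captures them. Present Kaplan-Meier curves and the unadjusted log-rank test as supporting. If a statistical analysis plan already names such a model, align the protocol sentence with it.

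The cost is a sentence or two of wording. The respiratory values need no new data. The estimate becomes a conditional hazard ratio, which is why the unadjusted result should stand beside it. If the covariates turn out not to be prognostic, at most about 2 points of power are lost.
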